### Products Used in the Intervention Groups

The electronic dispensers placed on the construction sites in the intervention groups will be filled with sunscreen Stokoderm® Sun Protect 50 PURE SPF 50 UV skin protection lotion for professional use. This product is a cosmetic product regulated by and complying with Regulation EC no. 1223/2009 (as amended) on Cosmetics Products. The main ingredients are ethylhexyl salicylate, bis-ethylhexyloxyphenol methoxyphenyl triazine, butyl methoxydibenzoylmethane, octocrylene, and homosalate.

### Description of the Study Procedures and Intervention

The flowchart of the study design is shown in Figure 1. During the recruitment phase, the researchers will visit the construction sites. The construction workers will be informed on the study protocol in both oral and written form by the investigator. Written informed consent will be obtained. The suitability of the construction worker to participate in the study will be checked using the inclusion criteria, as mentioned before (in section Participants and Recruitment). Construction workers fulfilling the criteria will be enrolled in the study.

**Figure 1 F1:**
[figure not shown]
Flowchart of the study design.

The researchers will visit the worksites of the intervention and control groups three times (at T = 0, T = 6 weeks, and T = 12 weeks). The participants will be asked to fill in a questionnaire at the start (T = 0) and the end of the study (T = 12 weeks). At T = 0, T = 6 weeks, and T = 12 weeks, stratum corneum (SC) samples will be collected, and measurements of personal UV-exposure by using personal dosimeters will be performed during work shifts for 1 week (Monday to Friday). At the end of the study (T = 12 weeks), the participants will undergo a skin check of the sun-exposed body parts for the presence of AK and NMSC by a trained investigator (physician). The intervention and control groups will receive basic information (i.e., a 15-min Powerpoint presentation) on the nature of the study and sun-safety and UV-protective behavior at the beginning of the study (baseline).

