
Several gaps in the current knowledge are to be filled, these are the prevalence of NMSC including AK, the occupational UV-exposure, and ultimately the effectiveness of an intervention aimed at increasing of sunscreen use in outdoor workers. Well-designed and sufficiently powered studies with adequate adjustment for confounding factors are required to provide more accurate risk estimates for occupational NMSC (23). Data on UV-exposure (external and internal, i.e., the UV-dose that reaches the surface of the skin and the UV-dose absorbed by the skin, respectively), presence of NMSC (including AK), and sunscreen use in outdoor workers in the Netherlands are not yet available.

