### Power Calculation

The study is planned to include 200 participants. The sample size is based on the expectation regarding the change in sunscreen usage. There is no available data on sunscreen use in outdoor workers in the Netherlands, or the barriers for sunscreen use. Therefore, we based our calculations of the sample size on a Canadian study reporting that 25% of the outdoor workers used sunscreen regularly (47). We assumed that 25% of the outdoor workers in the control groups will use sunscreen, and that in the intervention groups we expect this percentage will increase up to 50%. To calculate the sample size, nQuery Advisor software (Statistical Solutions Ltd, Boston, MA, U.S.A.) was used (proportion, two groups, two-sided test). A sample size of 58 workers per group will have 80% power to detect a difference in proportion that equals at least 0.05 significance level. Taking into account possible drop-outs, 100 outdoor workers per group will be recruited.

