### Statistical Methods and Data Analysis

There will be no replacement of any individual subjects who withdraw. However, the characteristics (e.g., job task, age) and number of withdrawals will be monitored.

The characteristics of the construction workers (e.g., age) and job tasks will be presented by using descriptive statistics. We will use the mean and standard deviation to describe normally distributed continuous variables and the median and interquartile range to describe non-normally distributed continuous variables. For the self-reported sunscreen usage data (primary outcome), counts and percentages to present categorical variables will be used. The self-reported sunscreen usage data will be dichotomized and analyzed by Chi-squared statistical test to establish whether sunscreen consumption will differ between the intervention and control groups. Two-sided *p*-values of <0.05 will be considered statistically significant and statistical uncertainty will be expressed using two-sided 95% confidence intervals. For the main study parameter, intention-to-treat analysis will be performed.

For the secondary study parameters we will present the levels of biomarkers and the number of sunburn episodes as quantitative, continuous variables. The biomarker levels at T = 6 weeks and T = 12 weeks will be compared with the baseline levels using paired ANOVA test followed by the correction for multiple testing, dependently on the distribution of data. The presence of NMSC including AK will be presented as counts and percentages.

UV-exposure measured by UV-dosimeters will be presented per job task, and as average of the measurements by all workers who worn the dosimeter in the same period. Data will be presented as average dose per day. Furthermore, the UV-exposure pattern during the work shift will be revealed.

The distribution will be tested by using Shapiro-Wilk normality test.

Before data analysis, a detailed data analysis plan will be available.

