Recently, a randomized control crossover trial in the United Kingdom (48) which aimed to reduce UV-exposure in the summer, found outdoor workers were exposed to relatively high UV levels in the summer. From the measured UV-dose, approximately a two-fold increase in the risk of being diagnosed with NMSC could be expected if the exposure continued their whole life. The intervention was based on increasing awareness by sending daily messages on the smartphone with recommendations for appropriate measures to reduce UV-exposure. However, this intervention failed to reduce exposure to UV (48). Another study in the United Kingdom found a slight (non-significant) change in sun protective behavior in construction workers after showing them an educational video (49). Our study is focused on reducing internal UV-exposure by using sunscreen. To remove possible barriers such as availability, accessibility, and the costs of sunscreen (10, 21, 22), we provide sunscreen dispensers placed at easily accessible places. Furthermore, we will electronically monitor the amount of sunscreen used, and provide regular feedback on sunscreen use by means of posters. In general, monitoring and feedback are widely used as a strategy to induce behavior change and have been shown to be effective when baseline performance is low, and it is provided more than once (50). Also group monitoring is recognized as being more effective than monitoring systems based on tracking individual actions which do not exploit the stimulating effect of group coherence (50). However, a recent systematic review found that there is very low quality evidence that company-oriented safety interventions reduce injuries among construction workers, and action is needed to increase the adherence of construction workers and employees to protection measures (51).

Strong points of this study are the real-time monitoring of sunscreen use, facilitation of sunscreens, feedback on sunscreen use, and the objective assessment of external and internal UV-dose by using, respectively UV-dosimetry and biomarkers of UV-dose. Also, assessment of the prevalence of NMSC including AK in outdoor workers by a physician will provide evidence on the prevalence of occupational skin cancer in construction workers.

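### The stated biomarker test compares workers only with their own baseline, so it cannot tell a change in UV exposure between visits from sunscreen protection

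*Protocol article*

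**What the plan says.** The Introduction separates external from internal exposure: "the UV-dose that reaches the surface of the skin and the UV-dose absorbed by the skin". The Discussion puts the aim on the second: "Our study is focused on reducing internal UV-exposure by using sunscreen". It also lists change in biomarkers from baseline to weeks 6 and 12 among the data from which effectiveness will be judged.

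Under Description of the Study Procedures and Intervention, "The researchers will visit the worksites of the intervention and control groups three times", at T = 0, 6 and 12 weeks. Skin samples are collected at those time points, and "measurements of personal UV-exposure by using personal dosimeters will be performed during work shifts for 1 week (Monday to Friday". The UV-Dosimetry section limits the dosimeters to 10 workers per group, chosen to cover as many job tasks as possible.

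Statistical Methods and Data Analysis gives two separate treatments:

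- Biomarkers at weeks 6 and 12 are compared with baseline by a paired ANOVA with a correction for multiple testing. No between-arm comparison and no exposure term is stated.
- Dosimetry is presented per job task and as the "average of the measurements by all workers who worn the dosimeter in the same period".

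The only planned link with UV exposure is in Process Outcomes. It concerns dispenser use in the intervention groups, not the biomarkers.

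**The concern.** A biomarker of absorbed dose depends on two things: how much UV reached the skin and how much the sunscreen stopped. The section on markers of internal UV-dose says as much, describing the cis isomer as formed by UVB in a dose-dependent way up to a plateau at about 60–70% of total urocanic acid. A comparison of each worker with his or her own baseline removes stable personal differences. It does not remove a change in exposure between visits, and May to July is a period in which such change is to be expected.

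The stated test could therefore credit the intervention with a fall in the marker that came from a cloudy measurement week or more indoor work. It could equally miss real protection because the later visits were sunnier. The control sites are sampled on the same schedule and could separate the two, but the stated analysis does not use them for this. This is a stated method that does not serve its stated use, rather than a detail left for later.

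**Working it through.** **1. The plan's own figure.** The only sample-size figure concerns the primary outcome: 25% in the control groups, and "in the intervention groups we expect this percentage will increase up to 50"%, with "A sample size of 58 workers per group will have 80% power" and, from Statistical Methods, "Two-sided *p*-values of <0.05 will be considered statistically significant". With the pooled two-proportion formula and mean proportion 0.375:

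n = [1.960 × √(2 × 0.375 × 0.625) + 0.842 × √(0.25 × 0.75 + 0.50 × 0.50)]² / 0.25² = 57.7, rounded up to 58.

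It reproduces and is untouched by this point. The protocol gives no SD, effect size or correlation for the biomarkers, so everything below rests on labelled assumptions.

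**2. What each comparison cancels.** Assume the marker is roughly proportional to dose below its plateau. For one worker, marker = k × D × (1 − p), where k is a personal constant, D the external dose and p the fraction stopped by sunscreen. Write subscripts 0 and t for baseline and follow-up.

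- *Within person:* ratio = (D_t / D_0) × (1 − p_t) / (1 − p_0). The constant k cancels, and so does a site difference in D that is the same at both visits. The change D_t / D_0 does not cancel.
- *Between arms, in log change:* any D_t / D_0 common to both arms also cancels. Only a change in exposure that differs between arms remains.

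With no sunscreen at baseline (p_0 = 0) and an assumed true protection of 30%, the within-person ratio is 1, meaning no visible change, when D_t / D_0 = 1 / 0.70 = 1.43. A 43% rise in dose between visits hides the effect completely. With no protection at all, any fall in dose appears in full as a fall in the marker.

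**3. Error rate of the stated test.** Suppose exposure alone moves the mean marker by δ SD of the within-person change, with zero sunscreen effect and n independent workers in one arm. Then P(significant) ≈ Φ(δ√n − 1.96).

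- δ = 0.25, n = 100: 0.25 × 10 = 2.50, and Φ(0.54) = 0.71.
- δ = 0.25, n = 58: 0.25 × 7.62 = 1.90, and Φ(−0.06) = 0.48.
- A Bonferroni correction for the two follow-up visits (critical value 2.24) lowers the first only to Φ(0.26) = 0.60.

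**4. What remains after a between-arm contrast.** Let the arms differ by g SD in change of exposure, with correlation r between that change and change in the marker. The spurious difference is r × g SD.

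| g | r | Spurious difference | P(significant), 100 per arm | P(significant), 58 per arm |
|---|---|---|---|---|
| 0.2 | 0.3 | 0.06 SD | 0.07 | 0.06 |
| 0.5 | 0.5 | 0.25 SD | 0.42 | 0.27 |
| 0.8 | 0.7 | 0.56 SD | 0.98 | 0.85 |

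The contrast removes the shared seasonal change but not a divergence between sites, so a supporting dose adjustment is still worth having. These figures ignore clustering by site.

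**5. What dose adjustment can deliver.** Ten wearers per group means 4 × 10 = 40 if *group* is a site and 2 × 10 = 20 if it is an arm. The detectable difference at 80% power is (1.960 + 0.842) × √(2/n) × √(1 − r²), where r is now the correlation between dose and marker.

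| Wearers per arm | r = 0 | r = 0.5 | r = 0.7 |
|---|---|---|---|
| 20 | 0.89 SD | 0.77 SD | 0.63 SD |
| 10 | 1.25 SD | 1.09 SD | 0.89 SD |

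Individual dose adjustment is therefore too imprecise to carry the main biomarker conclusion.

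**The case against.** Three arguments on the other side carry weight.

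- *The design already limits exposure differences, and a data analysis plan is promised.* Sites are matched on worksite and job tasks, location and time-frame, and a less-exposed skin site is also sampled. Matching helps a between-arm contrast, but none is stated for the biomarkers, and it does nothing for change over time within a worker. No analysis of the less-exposed site as a control is stated. An unlisted covariate would indeed be a matter for the analysis plan. A stated test that does not answer the stated question is not.
- *Adjusting for dose at weeks 6 and 12 is itself debatable.* This stands. The measurement is post-intervention, and the feedback posters may change behaviour outdoors. It covers work shifts only and is taken on the upper arm, while the sample comes from the forehead. The marker also plateaus. Dose adjustment therefore belongs in a supporting role.
- *External dose is not wasted as planned.* It is a study objective and a secondary outcome in its own right. This also stands.

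A reader might go further than the document allows in three ways:

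- That both doses are measured in the same workers throughout. Only 10 purposively chosen workers per group wear a dosimeter.
- That the skin sample misses the monitored week. The article gives no sampling day and does not say that a visit lasts one day. The flowchart is not shown, and the full protocol may settle it.
- That a standing difference in dose between sites would pass for protection. Under proportionality it is present at baseline too and cancels in the stated comparison.

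**Conclusion.** The point holds for the analysis. The biomarker comparison as stated cannot separate sunscreen protection from a change in exposure between visits, although the Discussion relies on it as evidence of effectiveness. The direction of the bias is unknown. On the assumptions shown, an exposure-driven shift of 0.25 SD is declared significant in about 0.71 of studies with 100 workers in the arm tested (0.48 with 58), against a nominal 0.05. These rates illustrate the mechanism and are not estimates for this trial, because the protocol gives neither the variability of the markers nor their correlation with dose.

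The point does not extend to fixed site differences in dose, nor to a claim that sampling and dosimetry fail to overlap. It concerns a secondary outcome and leaves the primary analysis and its 58 per group unaffected. The change is worth making before recruitment, because it needs no new data.

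**What to change.** **Main change.** Replace the paired comparison, as the effectiveness analysis, with a mixed model of the biomarker, for example the log of the cis share of total urocanic acid, cis/(cis + trans). Use weeks 6 and 12 as outcomes, with arm, visit and their interaction, the baseline value as covariate, and a worker effect. Report the between-arm difference in change with its 95% confidence interval at each visit. Since sites are not randomised and baseline is measured with error, also show the simple difference in change as a check. Keep the within-person comparison as description.

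**Supporting analysis.** Add the external dose of the same week: personal dose in the wearers, and a site-week or job-task mean for the others where enough wearers exist to form one. Report adjusted and unadjusted results together, and state whether 10 per group means per site or per arm.

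**Cost.** Text in the analysis plan and modest analysis time, on data already to be collected. The dose-adjusted estimate will be imprecise (about 0.9 SD detectable with 20 wearers per arm and 1.25 SD with 10, before any gain from the covariate). It adjusts for a post-intervention measurement and applies an upper-arm, work-shift dose to a forehead sample. With two sites per arm, the main contrast also remains a comparison of few sites and should be worded accordingly.

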#### Questionnaires

The questionnaire will include questions about age, gender, country of origin, work status as outdoor worker and job characteristics (e.g., job task), number of years in current profession and previous jobs, sun-related risk knowledge, attitudes, barriers for using sunscreen, outside leisure-time spending, and UV-protective behaviors (e.g., use of sunscreen). In the closing questionnaire (T = 12 weeks) an additional question about the number of sunburn episodes during the study period will be included. In the intervention groups questions about satisfaction with the provided sunscreen and their opinion about the effectiveness of the feedback posters will be added (see Intervention Groups: Sunscreen Dispensers and Feedback Posters).

#### UV-Dosimetry

A limited number of participants in all groups (*n* = 10 per each group) will wear a UV-dosimeter during their work shift during 1 week at each time point (T = 0, T = 6 weeks, T = 12 weeks). The selection of outdoor workers who will wear the dosimeters will be performed in way that ensures a maximal variability of job tasks. The Scienterra UV-dosimeter, which will be used in the present study, has proved to be a reliable method to measure external UVB-exposure in outdoor workers (25), and has been used previously to study the influence of human behavior on personal UV-exposure (26). The personal UV-dosimeter will be worn on the left upper arm, which has shown to be a reliable, practical and convenient body site in a previous study (27), and it will not interfere with work tasks.

#### Collection of SC Samples: Procedure of Tape Stripping

During the study, SC samples will be collected at the beginning (T = 0), half-way (T = 6 weeks), and at the end of the study (T = 12 weeks) in both groups. The SC will be collected by using adhesive tape strips with a minimally invasive, non-painful method which is extensively used in experimental studies (28–30). Adhesive tape discs (3.8 cm^2^, D-Squame; CuDerm, Dallas, TX, USA) will be attached to the skin. Each tape is pressed on the skin for 5 sec with standardized force, using a disc pressure applicator (CuDerm). The tape strips will be removed gently with tweezers and stored in a closed vial at −80°C until analysis. The samples will be taken from skin sites exposed to the sun (i.e., forehead), and a less-exposed skin site (i.e., behind the ear).

#### Analysis of the Markers of the Internal UV-Dose

The markers of the internal UV-dose will include the *cis-* and *trans-*isomers of urocanic acid (UCA), and immune markers of different signature such as matrix metalloproteinases (MMP), cytokines, and angiogenesis factors. The isomers of UCA are one of the most studied UVR-related biomarkers (31–34). *Trans*-urocanic acid (tUCA) is a major UVR-absorbing component in the epidermis and it isomerizes to the *cis-*form (cUCA) upon exposure to UVB in a dose-dependent manner until reaching a photo stationary state at ~60–70% of total UCA (35). That makes cUCA a very specific marker as it is not endogenously present but is formed upon exposure to UVR (36). Immunological markers have been proposed to assess the effects of UVR-exposure (37–40), as the adverse effects of UVR might have occurred before visible changes occur (erythema of the skin), and furthermore, immune response in the skin plays an important role in UVR-mediated damage (41). Immunological markers might be in particular useful to assess repeated exposure to UVR (29).

The markers will be extracted from the tape using a buffer, and subsequently analyzed using an appropriate technique. For urocanic acid, HPLC (High Performance Liquid Chromatography) method will be used, and for cytokines the multiplex immuno-assay (MSD–Meso Scale Discovery LLC, Maryland, U.S.A.). For all analyses, standard operating procedures (SOP) will be used. The analysis of the markers will be performed blinded, the samples will be coded untraceable to the participants (the codes will be open after data analysis has been performed).

#### Skin Check

At the end of the study (T = 12 weeks), a skin check of the sun-exposed skin by a trained investigator (physician) will be performed on the participants of all groups. Besides examination for NMSC and AK, following clinical features (42), skin photo type following Fitzpatrick (43) will be recorded. Furthermore, skin photo damage will be assessed by the validated Glogau photo damage classification scale (44).

#### Intervention Groups: Sunscreen Dispensers and Feedback Posters

The intervention groups will be provided with electronic sunscreen dispensers (with monitoring system) installed at the construction site at readily accessible strategic places (canteen/offices etc.). The electronic dispenser, equipped with a Wi-Fi transmitter, continuously records each application event, providing information on the timing and frequency of sunscreen use during the work shift. The system provides robust and easy to interpret web-based reports on sunscreen use per dispenser. Data on use pattern (frequency, total consumption, moments of use) and trends will enable structured feedback on sunscreen use to be given to the construction workers to motivate and improve compliance. Feedback on sunscreen use will be provided using posters placed in proximity of the dispensers, and will be replaced with actual data every 2 weeks. To increase the readability and understanding of the information on the posters, visual aids will be used when possible. Recent systematic reviews found that processing a message in a colorful and illustrative format transmits the message more effectively (45, 46). Also, with the increase of foreign nationals in construction, the use of visual means for conveying health and safety messages is widely popular (45).

### Outcome Measures

#### Primary Outcome

The individual frequency of sunscreen use will be derived from the questionnaires. When asked how often sunscreen is applied on a daily basis in the last month, the answer options are “never, seldom, sometimes, often, always.” Difference in the frequency of sunscreen use between the intervention and control groups will serve as the primary outcome.

